#### UCPPS Education

EDU is delivered in four 50–60-min individual clinic sessions and structured around information dissemination, support, and reflection. Content includes information about chronic pelvic pain and its clinical features, epidemiology, diagnostic criteria, medical tests, and treatment options as well as the role of stress, diet, and physical activity (Table 2). To control for home exercises of MC-CBT, subjects receive a science-based pelvic pain education book [92] that emphasizes the therapeutic value of knowledge ("the more you know about pain, the better off you'll be"), track UCPPS symptoms (but not corresponding thoughts, behaviors, and emotions), and complete a stress profile [93] without prescriptive behavior changes overlapping with CBT.

#### Explanation of choice of comparators

EPPIC’s UCPPS Education (EDU) condition conforms to the best practice [67, 94] of a nonspecific comparator structurally equivalent to MC-CBT (credibility, time, attention, therapist training, etc.). By comparing CBT to a non-specific education condition, we will be able to discern whether treatment effects reflect the benefits of specific CBT’s technical components above and beyond the generic effects of simply going to treatment that comes from feeling listened to and receiving support, mobilizing positive expectancy for improvement, establishing a therapeutic relationship around working toward shared goals with a trusted and knowledgeable clinician.

### Sequence generation, concealment, and implementation

Simple randomization into one of the two equal-probability conditions in a 1:1 ratio on a continuous basis as participants qualify for allocation will be performed by the study coordinator who has no patient care responsibilities as a safeguard against selection bias. In addition, treatment assignment will be conducted using Randomization Module in Research Electronic Data Capture (REDCap) software [95], which *generates* random and unpredictable sequence of assignments. The details of its computer-generated randomization algorithm are unknown to members of the EPPIC research team. Allocation sequence *concealment* from study personnel is achieved because REDCap conceals the next treatment assignment from being known. In other words, neither participants nor members of the research team are aware of the generated sequence until (and only for) the participant is assigned to his/her respective condition. Allocation sequence is generated by a computer independent of research coordinator who *implements* the assignment. Because the two treatments have identical dosages (4 sessions), the condition to which the participant is assigned is not revealed to him/her until session 1 of the acute phase, further minimizing selection bias.

### Concomitant care policy

To optimize the external validity of study findings and expedite accrual, participants of both conditions will be permitted to continue with or modify the treatment they were engaged through the acute phase with exception of ongoing pelvic pain-targeted psychological therapy which is disallowed for allocation. To strike a balance between methodological (rigor) and ethical (safety) concerns, patients will be encouraged to maintain concomitant care use during the baseline period for the purpose of establishing a stable reference for gauging treatment effects. It is our policy that an outright requirement of maintaining a stable dose through the baseline period exposes the participant to an unjustified level of risk should s/he experience a serious health event for which a change in medications or other therapies is medically necessary for and represents a higher order consideration than internal validity. Because the likelihood of serious health events is expected to be low for this population, encouraging patients to maintain stable doses through the baseline period does not diminish rigor and may actually increase participant engagement that optimizes overall internal validity. We also believe that our approach results in a more representative sample that includes participants with medical comorbidities for which medications are often prescribed. Beyond ethical issues, stabilizing concomitant therapies during the acute treatment phase may distort the therapeutic benefit of a self-management treatment for participants who learn to control symptoms for which they no longer require pharmacological, rehabilitative, or dietary interventions reported at baseline. A stronger methodological approach is to assess concomitant health care (e.g., dosage, type) which we will capture via self-report, factor into statistical analyses, and present in the final report.

### Blinding

A board-certified urologist or urogynecologist will confirm medical eligibility using formal diagnostic criteria for IC/BPS or CP/CPPS at baseline for all patients and function as independent evaluators (“blind” to treatment assignment) of symptom improvement at immediate (week 12), 3 months and 6 months follow-ups. Participants will be unaware of study hypotheses and blind to treatment assignment through the pretreatment baseline period. The methodological criterion of blinding participants to assigned treatments is inapplicable to behavioral interventions [96]. To the extent that blinding controls for differential expectations and consequent demand characteristics they may generate, we will adopt the established, surrogate practice [96, 97] of having participants rate the credibility and expectancy of improvement of the treatment to which they were assigned using the Credibility/Expectancy Scale [98] at the end of session 1 (week 1). Statisticians will be blinded to treatment allocation during the study by analyzing deidentified data until data is unlocked [99].

### Retention and compliance

To optimize session patient retention and compliance, we will provide reminders via their preferred method of text, telephone call, or email within 1 business day of the scheduled appointment. We will provide an honorarium for travel, time, and convenience for assessments: Initial assessment ($25); interim ($25); and 2 weeks ($50), 3 months ($50), and 6 months ($50) follow-ups. Patients who complete 75% of sessions will be regarded a priori as having received a clinically thorough regimen of treatment to which they were assigned (e.g., compliers). Additional strategies are codified in a retention plan that covers areas such as staff training for initial contact, early detection of patient behaviors that may “red flag” correctable adherence problems (e.g., work conflict), formal training in rapport building, and positive staff-patient communication skills, creating a welcoming and respectful environment for participants, and educating participants about their role as participants and the role of participation incentives. Other procedures to minimize attrition and non-adherence include engendering trust, maintaining relevance to clients’ needs, establishing routine while maintaining a degree of flexibility in scheduling to maintain engagement in both treatment and assessment phases of a study, therapist techniques for “rolling with resistance”, and other brief motivational enhancement strategies that are uniformly applied across conditions and therefore do not represent a source of bias. Secondary indices of compliance include the number of no-shows (failing to show without contacting office), and canceled appointments without rescheduling. Compliance with weekly home exercises will be measured using a 6-point clinician rating scale ranging from 1 (0%) to 6 (>100%) [48, 100]. For participants who prematurely discontinue treatment (dropouts), we will identify self-reported reasons for withdrawal and record them. Reason(s) for dropout will be coded using five categories: logistical (e.g., childcare coverage), treatment/program related (e.g., participant prefers different treatment, stopped because they felt better, it failed to meet their needs, not the right time to engage in treatment); influence of others (e.g., treating doctor advised against continuing); study staff reasons (e.g., eligibility failure due to non-disclosure of information that would have rendered patient ineligible); miscellaneous (e.g., death). Participants who discontinue treatment will be encouraged to complete follow-up assessments in an effort to optimize intent to treat (ITT) analyses.

### Treatment fidelity

To optimize the quality of and adherence to CBT and EDU, therapists will receive extensive training in the components of each treatment under expert supervision before being assigned to study patients. Delivery will be optimized by treatment manuals that provide detailed session-by-session guidance to standardize intervention across therapists; the completion of checklists for session protocols after each session; and regularly scheduled supervision with senior clinicians. Sessions will be audio taped, 25% of which will be randomly selected per patient and rated for protocol adherence by an independent rater unassigned to treatment delivery.

### Data collection and management

#### Primary outcome measure

The patient version of the Clinical Global Impressions - Improvement Scale (CGI-I) is a 7-point centered scale that integrates symptom severity and improvement over time as the primary outcome measure. Specific UCPPS-based anchors points for rating the CGI will be appropriately added as is the convention for other multi-symptom disease states [101] including chronic pelvic pain [102]. Global ratings of UCPPS symptom improvement yield a measure of overall multi-symptom benefit from treatment and is a core outcome domain in pain RCTs [103]. Those who score 2 (much improved) or better at follow-up qualify as categorical responders. Patients will complete the CGI at the three follow-up assessments and, for process analyses (Aim 3), weeks 3, 5, 7, 8, and 10 of the acute phase. The clinician version of the CGI will be completed at follow-up by “blind” MDs masked to treatment assignment to minimize bias and establish the validity of the patient version [48].

#### Secondary outcome measures

Secondary outcome measures include pelvic pain, urinary symptoms, pain interference, emotional distress, quality of life, and patient satisfaction using measures with confirmed psychometric properties (see Table 3). Severity of urinary symptoms and pelvic pain will be assessed using factorially derived items from the Genitourinary Pain Index (GUPI) [104] and the Interstitial Cystitis Symptom (ICSI) and Problem Indices (ICPI) [105]. Pain interference will be assessed using the PROMIS - Pain Interference scale (PPI SF-6a) [106], a 6-item instrument of the consequences of pain on relevant aspects of one’s life, including social, cognitive, emotional, physical, and recreational activities. Emotional distress will be measured using the Brief Symptom Inventory-18 (BSI-18) [107] which measures the level of distress across three dimensions (i.e., anxiety, somatization, and depression). The Client Satisfaction Questionnaire (CSQ) [108], an 8-item instrument measuring patient satisfaction with treatment, will assess the quality of care at immediate post treatment. Quality of life and co-morbid COPCs will be measured with the 12-item version of the SF-36 Health Status Questionniare [109] and 41-item Complex Multi-Symptom Inventory (CMSI) [110] respectively. UCPPS symptom measures (GUPI, ICPI, ICSI) will be assessed at baseline, interim (weeks 3, 5, 7, 8, and 10 of acute phase), and at all follow-up visits. As non-urological secondary outcomes, the BSI-18, CSQ, CMSI, SF-12, and PPI SF-6a will be measured at baseline and post treatment.

**Table 3 Tab3:** Enrollment, intervention, and assessment schedule for primary outcomes, mediators, and predictors

	Screening	BL	Acute phase						Follow-up		
Timepoint (week)	−2	0	1	3	5	7	8	10	12	22	34
**Enrollment:**											
Eligibility confirmation	x										
Informed consent	x										
Allocation		x									
**Interventions:**											
Minimal-contact CBT (MC-CBT)			**X**	T	**X**	T	**X**	**X**			
UCPPS Education			**X**	T	**X**	T	**X**	**X**			
**Assessments:**											
*Primary outcome*											
Global symptom improvement (CGI-I)				x		x	x	x	x	x	x
*Secondary outcomes*											
Emotional distress (BSI-18)		x							x	x	x
Patient satisfaction (CSQ)									x		
Comorbid COPCs (CMSI)		x							x	x	x
Pelvic pain severity (GUPI)		x		x		x	x	x	x	x	x
Urinary problem severity (ICPI)		x		x		x	x	x	x	x	x
Urinary symptom severity (ICSI)		x		x		x	x	x	x	x	x
Pain interference (PPI SF-6a)		x							x	x	x
Quality of life (SF-12 v2)		x							x	x	x
*Mediators*											
Perspective broadening (CERQ-PB)		x		x					x	x	x
Self-distancing (EQ-D)		x		x					x	x	x
Perceived control (MAIA-2)		x		x					x	x	x
Repetitive thinking (PTQ)		x				x			x	x	x
Context sensitivity (CSI)		x					x		x	x	x
Coping flexibility (CFS-R)		x						x	x	x	x
*Prescriptive predictors (moderators)*											
Trait self-regulation (BRIEF-A)		x									
*Prognostic predictors*											
Comorbidities: medical and psychiatric		x							x	x	x
Concomitant treatments		x							x	x	x
Demographics, chronicity, etc.		x									

*BL* baseline, *CGI-I* Clinical Global Impression-Improvement, *BSI-18* Brief Symptom Inventory-18, *CSQ* Client Satisfaction Questionnaire, *CMSI* Complex Medical Symptoms Inventory, *GUPI* Genitourinary Pain Index, *ICPI* Interstitial Cystitis Problem Index, *ICSI* Interstitial Cystitis Symptom Index, *PPI SF-6a* PROMIS - Pain Interference SF-6a, *SF-12 v2* Short Form-12 Health Survey v2, *CERQ-PB* Cognitive Emotion Regulation Questionnaire-Perspective Broadening, *EQ-D* Experiences Questionnaire-Decentering, *MAIA-2* Multidimensional Assessment of Interoceptive Awareness-2 (Noticing, Non-Distracting, Not-Worrying and Attention Regulation scales), *PTQ* Perseverative Thinking Questionnaire, *CSI* Context Sensitivity Index, *CFS-R* Coping Flexibility Scale-Revised, *BRIEF-A* Behavior Rating Inventory of Executive Functioning-Adult. Bolded Capped X = clinic session (intervention); T = telephone check in (intervention)

#### Mediators

The primary mediators are designed to tap into aspects of a rigid cognitive style central to a transdiagnostic conceptual model of centralized pain states such as UCPPS [111]. Mechanistic outcomes believed to drive CBT include context sensitivity, coping flexibility, repetitive thinking, self-distancing/perceived control, all of which are targeted by a different treatment module (see Table 2). All mediators will be assessed at baseline and follow-ups. The timing of additional mediator assessment is calibrated to the weeks when the corresponding skill believed to induce respective cognitive change is introduced and practiced. For example, because flexible problem solving is believed to improve symptom improvement by increasing sensitivity to contextual cues that promote coping (i.e., context sensitivity), the Context Sensitivity Questionnaire (CSI) [112] is administered at week 8 after the flexible problem-solving module is introduced and practiced. This approach differs from other assessment schedules of mechanistic studies when all putative mediators are assessed across different interim assessment periods (e.g., weeks 3, 5, 8) without regard to the mechanistic specificity of each strategy within a protocol [67]. By the same token, self-distancing, measured with the 11-item Experiences Questionnaire - Decentering (EQ-D) [113] and the Perspective Broadening scale of the Cognitive Emotion Regulation Questionnaire (CERQ-PB) [114] will be assessed at week 3 as will 4 scales (i.e., Noticing, Non-Distracting, Not-Worrying, Attention Regulation) of the Multidimensional Assessment of Interoceptive Awareness - 2 (MAIA-2) [115] measuring perceived control over aversive somatic sensations. Repetitive thinking will be assessed at week 7 and at all follow-ups with the Perseverative Thinking Questionnaire (PTQ) [116]. The Coping Flexibility Scale - Revised (CFS-R) [117], a 12-item instrument designed to measure discontinuation of ineffective coping strategies; re-coping, and meta-coping, will be assessed at baseline, week 10 and all follow-ups. Non-specific mediators common to both EDU and CBT include treatment expectancy (Credibility/Expectancy Questionnaire) [98] which will be assessed at the end of session 1 (week 1), while therapeutic alliance (Working Alliance Inventory) [118] which be assessed at weeks 1, 3, 5, 8, and 10.

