### Trial interventions

#### Minimal-contact CBT

MC-CBT involves four 50–60-min individual clinic sessions delivered over a 10-week acute phase. While descriptive content is tailored to UCPPS, the protocol synthesizes [69] evidence-based CBT strategies into 4 modules targeting core transdiagnostic vulnerability factors [70–73] reflecting a rigid cognitive style expressed as discrete perceptual biases [74]. These include (a) a tendency toward self-immersive, abstract, and repetitive negative thought (RNT) [70] manifested in (b) the inclination to overestimate the probability of negative events (threat expectancy bias) [75–78]; (c) the tendency to inflate their costs or consequences when they occur (threat interpretative bias) [79–81]; (d) extreme negative self-schemas [82] (i.e., dysfunctional misconceptions or core beliefs like perfectionism [83–85]); and (e) a rigid, non-discriminative coping style characterized by an overreliance on control-oriented, problem-focused strategies deployed regardless of situational demands (e.g., controllability) [86–90]. Technical components include “real time” self-monitoring to generate a functional analysis of symptoms, their triggers, and responses across multiple domains (cognitive, emotional, somatic, behavioral), diaphragmatic breathing to reduce arousal and enhance personal control, worry control (e.g., evidence-based logic, decatastrophizing) to correct maladaptive information processing style, flexible problem solving, and relapse prevention skills to maintain gains after treatment discontinuation. MC-CBT content is introduced sequentially and reinforced through the provision of a workbook [91] with home exercises designed to facilitate skills acquisition. MC-CBT components and corresponding transdiagnostic processes are based on prior research with transdiagnostically designed CBT [47, 48] and refined through stakeholder involvement (e.g., patients, physicians, physcians assistants, and therapists) for the EPPIC. Contents addressed in of each week of treatment are presented in Table 2.

**Table 2 Tab2:** Content topics and transdiagnostic processes of MC-CBT and content topics of education/support by treatment session

Week	Schedule	MC-CBT content	MC-CBT transdiagnostic process	EDU content

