1	Clinic visit 1	Treatment orientation and rationale; Acute vs chronic pain; Central sensitization; Self-monitoring (functional analysis); Introduction to relaxation	Perceived control over aversive internal states; Self-distancing (“fly on the wall”); Perspective broadening; Negative reactivity	Treatment orientation and rationale Education about Chronic Pelvic Pain (CPP) Emphasize value of emotional support Acute vs chronic pelvic pain, Symptom monitoring
2	Self-directed (no contact)	Relaxation training; Real-time self-monitoring (functional analysis)	Perceived control over aversive internal states; Self-distancing (“fly on the wall”); Perspective broadening;	Reflective writing narrative (RWN) about CPP and its personal impacts
3	Self-directed (phone check-in 1)	Portable relaxation training; Real-time self-monitoring (functional analysis)	Perceived control over aversive internal states; Self-distancing (“fly on the wall”); Perspective broadening	Understanding CPP; Review RWN Central sensitivity and CPP
4	Self-directed (no contact)	Introduction to cognitive flexibility model	Perceived control; Maladaptive worry/rumination; Repetitive negative thought (RNT)	Symptom triggers (emotions, relationships, family, work, etc.) of CPP
5	Clinic visit 2	Prediction testing; Evidence-based logic	RNT: Expectancy bias/prediction error (“What if?”)	The role of stress and CPP Review personalized Stress Profile
6	Self-directed (no contact)	Decatastrophizing	RNT: Interpretative bias (“If only…”)	Tracking dietary and physical activity triggers
7	Self-directed (phone check-in 2)	Applying evidence-based logic vs decatastrophizing skills to meet situational demands	RNT: Expectancy bias/Interpretative bias; Context sensitivity	Review activity and dietary triggers Pain and the stress response
8	Clinic visit 3	Flexible problem-solving training	Coping flexibility; Context sensitivity	Diet, activity and CPP
9	Self-directed (no contact)	Flexible problem solving Schema (core beliefs) modification	Coping flexibility; Context sensitivity; Negative self-schema (e.g., perfectionism)	Integrate knowledge learned about personalized triggers with biopsychosocial model
10	Clinic visit 4	Maintenance/relapse prevention	Maintenance	Review biopsychosocial model of CPP

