**Fig. 2 Fig2:**
[figure not shown]
Randomized experimental trial model of mediation analyses

Also of interest in an RET is the significance and magnitude of paths linking each mediator to the outcome. For example, perhaps a path associated with coping flexibility is not significant, suggesting that, contrary to our assumptions, coping flexibility does not meaningfully elicit UCPPS symptom improvement. In this case, we might consider streamlining the program so that it is simpler by eliminating the flexible problem solving. We will conduct state-of-the-art dominance analyses that allow us to order the relative strength of paths from the mediators to the outcome variable [133].

*Analyses for Aim 1:* Evaluate the efficacy of MC-CBT for UCPPS as compared to a nonspecific control intervention (EDU) in relieving pain and related symptoms. *H1a* states: Patients randomized to MC-CBT will show greater global symptom improvement on primary endpoint (CGI) compared to those randomized to EDU. This hypothesis will be tested using a covariate-adjusted single degree of freedom contrasts at each time point (immediate posttest 2 weeks, 3 and 6 months) comparing MC-CBT versus EDU on the full-scale CGI. Standard covariates will include medication history, gender, age, and indicators of symptom severity as measured at baseline. *H1b* states: MC-CBT will be superior to EDU on key secondary endpoints including the severity of pelvic pain and urinary symptoms, and functional impairment at post treatment. The same analytic strategy for H1a will be applied to secondary endpoints. For secondary outcomes, available baseline data will be included as a covariate.

*Analyses for Aim 2:* Evaluate the durability of MC-CBT relative to EDU at 3 months and 6 months following treatment discontinuation. This will be tested using the same approach as Aim 1 that is focused on the immediate posttest but now it will be focused on the time points of 3 months and 6 months, separately. The group differences in effects at one time point can be compared to the group difference at another time point using a single degree of freedom interaction contrast with time as a within-subject moderator, using a robust estimator (e.g., Huber-White or bootstrapping).

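### Table 2 gives context sensitivity and coping flexibility the same treatment content, so the coping-flexibility path alone cannot show that flexible problem solving is dispensable

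*Protocol article*

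**What the plan says.** All references are to the protocol article.

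- *Mediators* lists the mechanisms as "context sensitivity, coping flexibility, repetitive thinking, self-distancing/perceived control, all of which are targeted by a different treatment module (see Table 2"). It then gives its reason for measuring the CSI at week 8: flexible problem solving is expected to help by raising sensitivity to context.
- *Minimal-contact CBT* describes "evidence-based CBT strategies into 4 modules targeting core transdiagnostic vulnerability factors". It does not name the four modules. Negative self-schemas are factor (d) of the five vulnerability factors listed there.
- *Table 2*, week 8, has the content "Flexible problem-solving training" and the process cell "Coping flexibility; Context sensitivity". Week 9 has the content "Flexible problem solving Schema (core beliefs) modification" and the processes "Coping flexibility; Context sensitivity; Negative self-schema (e.g., perfectionism"). Week 7, on choosing between evidence-based logic and decatastrophizing, also lists context sensitivity.
- *Table 3* schedules six mediator measures (CERQ-PB, EQ-D, MAIA-2, PTQ, CSI, CFS-R). None measures self-schema.
- *Data analysis: analysis of aims*, in the text after Fig. 2, supposes that the coping-flexibility path is not significant and adds: "we might consider streamlining the program so that it is simpler by eliminating the flexible problem solving".
- *Discussion* generalises the idea. A module that moves neither its matching mediator nor symptoms may be shortened, changed or dropped.

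**The concern.** Hypothesis 3a rests on pairing each procedure with one presumed mediator, and the stated product of the explanatory analysis is advice on which components to keep, strengthen or remove. That advice needs the pairing to be one-to-one. If one component acts on two measured mediators, a null path for one of them says nothing about the other. This is a separate matter from reading non-significance as absence of effect: even a precisely estimated zero for coping flexibility would leave open that flexible problem solving works through context sensitivity. At stake is a wrong conclusion about a component of the programme, not the efficacy result.

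**Working it through.** The plan gives no figure on this point to reproduce. The check is a cross-reading, followed by one illustration under stated assumptions.

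**Step 1. Mediators against content and timing (Tables 2 and 3)**

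| Target | Where Table 2 places it | Measure and week during treatment |
|---|---|---|
| Perspective broadening, self-distancing, perceived control | Weeks 1–3, self-monitoring and relaxation (perceived control also in week 4) | CERQ-PB, EQ-D, MAIA-2 at week 3 |
| Repetitive thinking | Weeks 4–7, cognitive work on worry | PTQ at week 7 |
| Context sensitivity | Week 7, worry-control skills; weeks 8 and 9, flexible problem solving | CSI at week 8 |
| Coping flexibility | Weeks 8 and 9, flexible problem solving | CFS-R at week 10 |
| Negative self-schema | Week 9, schema modification | None |

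The third and fourth rows contradict the claim of a different module for each mediator. The text contradicts it too: Mediators ties flexible problem solving to context sensitivity, while the analysis of aims judges the same component by coping flexibility. Measuring the CSI at week 8 and the CFS-R at week 10 does not separate the two, since Table 2 attaches both processes to the same content in both weeks.

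The last row shows a target with no measure. Schema work shares week 9 with continued flexible problem solving, and both come before the week-10 CFS-R. A change in CFS-R by week 10 therefore cannot be assigned to one of them.

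**Step 2. What the example would do if only context sensitivity mattered**

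Inputs: N = 240 × 0.88 ≈ 211 (12% not assessed, from the power section). Assumed, because the documents give no values: the component shifts both mediators by d = 0.5; only context sensitivity affects the CGI, with coefficient 0.5 and residual SD 0.85; the mediators' residual correlation r is 0.3 to 0.7. The model regresses the CGI on treatment and both mediators, without baseline covariates, with 2,000 simulated trials per setting.

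| r | Coping-flexibility path significant | Context-sensitivity path significant | Arm difference on coping flexibility significant |
|---|---|---|---|
| 0.3 | 5.5% | 100% | 96.0% |
| 0.5 | 5.1% | 100% | 94.9% |
| 0.7 | 5.0% | 100% | 95.6% |

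The first column is simply the type I error rate, as it must be when the true path is zero. The coping-flexibility path thus carries no information on whether the component works.

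**Step 3. Does a joint test lose anything here?**

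Under the same assumptions the noncentrality for the context-sensitivity path alone is N·b²·(1 − r²)/σ². At r = 0.7 this is 211 × 0.25 × 0.51/0.7225 = 37.2. For the joint 2 df test it is N·b²/σ² = 211 × 0.25/0.7225 = 73.0, whatever r is. The joint test is not weaker in this setting.

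**The case against.** The strongest reply is that the text sets no decision rule. The analysis-of-aims passage is a hedged example about future programme design, and the Discussion also looks at symptoms, not only at the mediator. Someone applying the example would in practice also see the context-sensitivity path, which is significant in essentially every simulated trial above. This stands. It means that about 95% (100% minus about 5%) is not a forecast of the trial dropping a useful component; it shows only that the illustrated inference is uninformative. It does not repair the mapping, which is wrong in current text.

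A second reply is that safeguards exist: dominance analysis, latent variables for inter-correlated measures, arm comparisons on each mediator separately, and lagged models. These deal with collinearity. None gives each component its own mediator, and a latent variable over the two measures would merge them, which points towards a joint judgement. Fig. 2 is not visible to this review, so how the two mediators are linked in the model is unknown. The contradiction between Mediators and Table 2 does not depend on it.

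A reader might infer that, with both mediators in one model, their shared effect is split so that neither path shows. The figures do not support that. Assuming coefficients of 0.20 each, with the power section's R² of 0.40 and 8 predictors and N = 211, two separate simulations found neither path significant in about 0.1–0.2% of trials at r = 0.5, 0.8–0.9% at r = 0.7 and 4–5% at r = 0.8.

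A reader might also infer that the effect of schema work will be credited to coping flexibility. The documents show only that it cannot be separated, not where it will appear. Nor do they name a schema module or promise to evaluate one; schema modification is a content line in week 9.

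**Conclusion.** The point holds as an internal contradiction with a limited consequence. The claim of a different module for each mediator conflicts with Table 2, and the step from a null coping-flexibility path to removing flexible problem solving does not follow on the protocol's own account of how that component works. Schema modification cannot be evaluated separately with the scheduled measures. These conclusions rest on the text alone; the 5% figure is an illustration that depends on the assumed case in which only context sensitivity affects the CGI.

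It would go too far to call the mediation analysis invalid. The path estimates and the dominance ordering remain reportable, Aims 1 and 2 are untouched, and only the component-level conclusions of Aim 3 need to change. The correction is worth making because those conclusions are the stated purpose of the explanatory analysis.

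**What to change.** 1. Correct the Mediators sentence to match Table 2: coping flexibility and context sensitivity share flexible problem solving, and context sensitivity is also targeted at week 7.
2. Base any conclusion about flexible problem solving on the joint (2 df) contribution of context sensitivity and coping flexibility, with the single paths reported as description. Because of the week-7 overlap, a positive joint result should not be credited to flexible problem solving alone.
3. Reword the example in the analysis of aims, and the Discussion sentence that ties each module to one matching mediator, in the same sense.
4. State that the contribution of schema modification cannot be evaluated separately from continued flexible problem solving.

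The cost is wording and one prespecified contrast on data already scheduled. The downside is a slightly less specific claim about each of the two mediators.
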